### Clinical outcomes

#### Primary outcome

Cardiorenal anemia syndrome (CRAS) is the primary outcome of this study and will be defined as a triad comprising heart failure regardless of ejection fraction, chronic kidney disease with estimated glomerular filtration rate <60mil/min/1.73m^2^ and anemia of <12 g/dl for women or <13 g/dl for men [1, 2].

#### Secondary outcomes

Secondary outcomes will include:

**All-cause mortality** is any death that will occur within follow-up irrespective of cause [2, 11, 17–19].**Heart failure hospitalization** is defined as any admission of which the cause-specific is heart failure [2, 3, 5, 6].**Worsening renal function**: is defined when there is a change in chronic kidney disease stage to lower stage than baseline or a need of a dialysis or both [20, 21].**Worsening anemia**: is defined when there is a change of hemoglobin level to lower level from baseline which will then need either blood transfusion or erythropoietin use or both [3, 5, 22, 23].

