### Sample size estimation

To estimate the sample size, the proportionate formula used in prospective cohort studies will be used as it has been adopted from Baraka et al., 2023 [16].

$$n={\frac{\left(Z_{\alpha }/2\sqrt{\left(\frac{r+1}{r}\right)p*\left(1-p*\right)}+Z_{\beta }\sqrt{\frac{p_{1}\left(1-p_{1}\right)}{r}p_{2}\left(1-p_{2}\right)}\right)}{{\left(p_{1}-p_{2}\right)}^{2}}}^{2}$$

$$p*=\frac{p_{2}+rp_{1}}{r+1}$$

Where by

r = ratio between the two groups

p1 = CRAS prevalence obtained from literature

p2 = expected prevalence of CRAS from the study

p1 –p2 = effect size

Zβ = standard normal variate for statistical power

Zα/2 = standard normal variate for significance level

The prevalence of CRAS in previous studies was 44.4% [2]

The prevalence of CRAS in this study is expected to be 40%

Therefore;

r = 1

p1 = 44.4%

p2 = 40%

p1 − p2 = 13%

Zβ = 0.84 for statistical power of 80%

Zα/2 = 1.96 for significance level of 95%

n = 226

Considering the 30% attrition rate adopted from previous study [2]

Therefore, the minimum sample size required to meet the objectives will be 300 patients.

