**Chronic kidney disease (CKD)**	Medical records/patient report	Known patient with CKD from medical records within 6 months retrospectively prior enrollment or when estimated GFR is <60mil/min/1.73m2 by CKD-EPI formula using serum creatinine level	Dichotomous, continous
**Dyslipidemia**	Medical records/patient report/blood sample	Evidence of dyslipidemia on medications from records or for unknown lipid status, when the total cholesterol ≥200 mg/dl, low-density lipoprotein cholesterol ≥130 mg/ dl, and high-density lipoprotein cholesterol < 40 mg/ dl for men or < 50 mg/ dl for women, and/or serum triglyceride level ≥150 mg/ dl	Dichotomous, categorical
**Diabetes**	Medical record/patient report/blood sample	Known patient with diabetes mellitus on medications from records or for unknown status, is when the random blood glucose is ≥11.1 mmol/L and glycosylated haemoglobin of ≥6.5%	Dichotomous, categorical
**Electrolyte imbalance**	Medical report/blood sample	Serum Na+ of <135mmol/L or >145mmol/L and/or serum K+ of < 3.5mmol/L or >5.5mmol/L	Continous
**Obesity**	Medical record/patient assessment	When the waist circumference of >94 cm for males or >88 cm for females; or calculated waist-hip ratio (WHR) of >0.9 for men or of >0.8 for women	Dichotomous, categorical

#### Objective 3

Aims to determine the outcomes of the cardiorenal anemia syndrome among the patients with heart failure within six months follow up period [2, 5, 7, 11, 25] Table 3.

**Table 3 pone.0292764.t003:** Summary and description of variables for the objective number 3.

Variable	Method of measurement	Operational definition	Level of measurement
**All-cause mortality**	Medical records or close relative through phone contact	Any death occurs within six month follow up irrespective of the cause of death	Dichotomous
**Heart failure hospitalization**	Medical record/patient report/assessment	admission of which cause-specific is heart failure	Continuous
**Worsening renal function**	Medical record/patient report/blood sample	When there is a change in Chronic kidney disease stage or a need of dialysis or both	Continuous
**Worsening anemia**	Medical record/patient assessment/blood sample	Change of hemoglobin level to lower level from baseline or a need of blood transfusion or erythropoietin use or both	Continuous

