### Data analysis

All completed questionnaires will be coded before entered into dataset on Microsoft excel. SPSS windows version 25 program (IBM SPSS, Chicago IL) will be used for data management and analysis [16]. Data will be classified as CRAS or non-CRAS groups. Data will be presented as means **±** standard deviations for continuous variables with normal distribution, or median and interquartile range for no-parametric (skewed) variables [1, 2, 13]. Categorical variables will be presented as frequencies and percentages. Socio-demographic variables and clinical correlates of cardiorenal anemia syndrome at baseline will be analyzed and compared using Pearson chi-squared test for the categorical variables, and independent student’s t-test for the continuous variables [1, 2, 9]. The clinical correlates including age, gender, alcohol use, smoking history, hypertension, obesity, diabetes, and dyslipidemia and iron deficiency will be analysed and compared by using univariate and multivariate logistic regression. Cox proportional hazards model will be used to analyze and compare the outcomes of CRAS. A two-tailed p—value of less than 0.05 will indicate statistical significance [2, 7, 13].

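### Worsening renal function is defined in the wrong direction in the outcomes section and with no direction in Table 3, and the two rules conflict

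*Protocol article*

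**What the plan says.** Worsening renal function is one of four secondary outcomes, with all-cause mortality, heart failure hospitalization and worsening anemia. The protocol article defines it twice.

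- **Secondary outcomes section:** "a change in chronic kidney disease stage to lower stage than baseline or a need of a dialysis or both".
- **Table 3 (Objective 3), operational definition column:** "When there is a change in Chronic kidney disease stage or a need of dialysis or both". The level of measurement is given as continuous.

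The first rule has a direction and a baseline reference. The second has neither.

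For worsening anemia, the Secondary outcomes section uses parallel wording: "a change of hemoglobin level to lower level from baseline". There, lower does mean worse.

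The Data analysis section says how the outcomes will be used: "Cox proportional hazards model will be used to analyze and compare the outcomes of CRAS".

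**The concern.** CKD stages are numbered so that a higher stage is worse disease. The article follows this convention: its exclusion criteria name stage 5 alongside renal replacement therapy. A change to a lower stage is therefore, read literally, an improvement. The word lower suits hemoglobin but reverses the meaning when applied to a CKD stage. Table 3 does not repeat the reversal, but it drops the direction altogether.

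What is at stake is the event indicator. A Cox model needs a yes/no event with a date, and here the rule that sets the indicator differs between two places in the same document. Improvement during follow-up is a realistic path. The inclusion criteria admit patients with acute heart failure and allow CKD to be established from serum creatinine at the index contact, so some patients may later be restaged to a better category.

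The continuous label in Table 3 adds a smaller inconsistency, because both written rules describe an event that either happens or does not.

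**Working it through.** No arithmetic applies. No stated sample size, power or event count depends on this definition: the sample size is built on CRAS prevalence ("p2 = expected prevalence of CRAS from the study"), and no rate of stage change is given anywhere. The check is to take each possible course and apply each rule.

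**Inputs**

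1. Rule A: Secondary outcomes section, a move to a lower stage than baseline, or dialysis, or both.
2. Rule B: Table 3, any change of stage, or dialysis, or both.
3. Direction of staging: the exclusion criteria place stage 5 at the renal replacement end, so a higher number is worse.
4. Intended meaning: the name of the outcome, worsening renal function.

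**Result for each course**

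| Course during follow-up | Rule A, literal | Rule A, if lower stage means lower function | Rule B, literal | Intended by the name |
|---|---|---|---|---|
| Stage 4 to 3, no dialysis (improves) | Event | No event | Event | No event |
| Stage 3 to 4, no dialysis (deteriorates) | No event | Event | Event | Event |
| Same stage, no dialysis | No event | No event | No event | No event |
| Dialysis needed | Event | Event | Event | Event |

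**Reading the table**

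- Rule A taken literally is wrong in both of the first two rows. It counts the improver and misses the deterioration short of dialysis.
- Rule B taken literally captures every deterioration but also counts every improver.
- The literal rules disagree with each other on the second row, which is the group the outcome exists to detect.
- If Rule A is read charitably, it matches the intended column throughout. It then disagrees with Rule B on the first row, so a conflict remains.
- The two rules agree and are right only if the reader supplies the direction in both places: reinterpreting lower in Rule A and adding a direction to Rule B.

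**Measurement level.** Every cell above is event or no event. Table 3 lists all-cause mortality as dichotomous but the other three outcomes, including this one, as continuous. For this outcome, the label does not fit either definition or the planned Cox model.

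**The case against.** The strongest answer is that nobody would be misled. Both places define a variable whose name says worsening, the Introduction lists worsening renal function among the poor outcomes of CRAS, and the stage change is paired with a need for dialysis. On that view lower stage is loose wording for lower kidney function, probably carried over from the hemoglobin definition. Likewise, under its row heading in Table 3, a change of stage naturally means a change for the worse.

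Much of this stands. The intended direction is not in doubt, and Table 3 misses no deterioration even when read literally. It does not remove the point. The operational definition column is the natural source for coding, and there the direction has to be supplied by the reader. The neighbouring row for worsening anemia does state one. No other section settles which rule governs.

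A reader might go further and infer that improvers will in fact be counted, and that the hazard ratio for CRAS versus non-CRAS is therefore biased. The document does not support that. Whether improvers are counted depends on whether the coder follows the wording or the name. Any effect on the hazard ratio depends on how often patients in each group improve and deteriorate, and the article gives neither rate. An illustrative misclassification percentage would need an assumed eGFR distribution, measurement variability, stage cut-points and a follow-up creatinine for every patient. None of these can be taken from the article, which plans monthly contact by phone or routine visit.

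The continuous label is shared with two other outcomes. It looks like a general slip in the table and adds no weight to the direction error.

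**Conclusion.** The definition is wrong as written and should be fixed. In the Secondary outcomes section the direction is reversed; in Table 3 it is absent. The two rules contradict each other, and both, read literally, count patients who improve.

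The consequence is possible misclassification of events in one of the four outcomes compared by Cox model. It rests on one assumption, that coding follows the text and not the outcome's name. The size and direction of any effect on the hazard ratio cannot be derived from the document. CRAS prevalence, the analysis of its clinical correlates and the sample size do not use this outcome and are unaffected.

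**What to change.** Use one definition, in the same words, in the Secondary outcomes section and in Table 3: change to a more advanced (higher-numbered) CKD stage than at baseline, or need of dialysis, or both. In Table 3, change the level of measurement for this outcome from continuous to dichotomous, analysed as time to first event, to match the Cox model.

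The cost is a wording change in two places and one table cell. No new data, visits or sample size are required. Because recruitment was already under way when the article was written, the wording should be settled before outcomes are coded, and any outcomes already coded should be checked against it.

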#### Follow-up procedure

Every patient will be followed up on monthly basis within 6-months via phone calls or during regular clinic visit. In case a participant is not reachable following 3 phone calls on 3 alternative days on every fourth week of follow-up month or during clinic visit. Failure to be reachable will indicate lost to follow-up.

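### Worsening anaemia has two incompatible definitions: a haemoglobin fall that needs treatment (Secondary outcomes), or a fall of any size or a treatment need (Table 3)

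*Protocol article*

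**What the plan says.** The protocol article defines worsening anaemia twice.

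- **Clinical outcomes, Secondary outcomes:** "a change of hemoglobin level to lower level from baseline which will then need either blood transfusion or erythropoietin use or both". The fall and the treatment need are joined, so both are required.
- **Study variables, Objective 3, Table 3:** "Change of hemoglobin level to lower level from baseline or a need of blood transfusion or erythropoietin use or both". The same elements are alternatives, so any one is enough. The method of measurement is "Medical record/patient assessment/blood sample" and the level of measurement is given as continuous.

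On follow-up, the Follow-up procedure section says: "Every patient will be followed up on monthly basis within 6-months via phone calls or during regular clinic visit". The article describes how blood is drawn and analysed, but gives no number or timing of repeat haemoglobin tests.

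On analysis, the Data analysis section says: "Cox proportional hazards model will be used to analyze and compare the outcomes of CRAS".

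**The concern.** A Cox model needs one event definition and an event date for each patient. Here the two rules classify a whole class of patients in opposite ways: those whose haemoglobin drops below baseline without a need for transfusion or erythropoietin.

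The Table 3 rule has a further difficulty. With no minimum fall, a 0.1 g/dl difference between two readings is an event, so ordinary fluctuation generates events. The more often a patient is retested, the more likely a lower reading becomes. Because contact may be by phone or at routine visits, the number of haemoglobin values may differ between patients and possibly between the CRAS and non-CRAS groups. At stake is whether the reported hazard ratio for this outcome can be interpreted, and whether the rule might be chosen after results are known. Recruitment had already begun when the article was written (92 patients, per the abstract).

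**Working it through.** **Step 1. The two rules side by side.**

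| Patient during follow-up | Secondary outcomes section | Table 3 |
|---|---|---|
| Haemoglobin falls, no treatment need | not an event | event |
| Haemoglobin falls, treatment then needed | event | event |
| Treatment needed, no fall recorded | not an event | event |
| No fall, no treatment need | not an event | not an event |

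The rules agree in two rows and disagree in two. Table 3 can only give as many events or more. The documents give no transfusion or erythropoietin rate, so the ratio of the two event counts cannot be calculated.

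**Step 2. How often Table 3 is met by chance.** The plan has no figure to reproduce, so this rests on an assumption: a patient with no true change has exchangeable readings. The baseline is then equally likely to hold any rank among the k + 1 readings, and the chance that it is the lowest is 1/(k+1). Hence

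P(at least one of k follow-up readings is below baseline) = 1 − 1/(k+1) = k/(k+1).

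- k = 1: 1/2 = 50%
- k = 2: 2/3 = 67%
- k = 3: 3/4 = 75%
- k = 6: 6/7 = 86%

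Six is the most that monthly contacts over six months could give, if each produced a blood test. The protocol does not say that they do.

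**Step 3. Allowing for rounding and low baselines.** The formula ignores ties. A simulation of 400,000 patients with no true change used values rounded to 0.1 g/dl. Its inputs are assumptions, not document figures: between-patient mean 12 and SD 1.8 g/dl, within-patient SD 0.3, 0.5 or 0.8 g/dl. Ranges run across the three within-patient SDs.

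| Follow-up values | Formula | Simulated, all | Simulated, baseline below 12.5 g/dl |
|---|---|---|---|
| 1 | 50% | 45–48% | 41–43% |
| 2 | 67% | 62–65% | 57–59% |
| 3 | 75% | 70–73% | 67–68% |
| 6 | 86% | 82–85% | about 80% |

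So about 41–50% with one value, 57–67% with two and 80–86% with six. The formula is a ceiling for patients not selected on their baseline value. Under the Secondary outcomes rule, none of these chance falls is an event unless treatment is then needed.

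**Step 4. Direction of bias.** CRAS is defined partly by low baseline haemoglobin, so regression to the mean enters the comparison. In the same simulation with one recheck, about 41–43% of patients with a baseline below 12.5 g/dl showed a fall, against 50–59% of the rest. That alone would make worsening look less common among patients with low baselines. If CRAS patients were retested more often, the effect would run the other way. The documents give no testing frequency by group, so the net direction is unknown.

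**Step 5. The variable type.** Each rule describes something that either happens or does not. Table 3 labels all-cause mortality dichotomous but worsening anaemia continuous, which fits neither rule nor the Cox analysis.

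**The case against.** The strongest reply is that the size of the problem is unproven. Four parts of it stand.

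- A reader might infer that most stable patients would qualify under Table 3. The documents do not support this, because the number of repeat haemoglobin values is never stated. With one recheck the share is about half or fewer, and a patient followed only by phone may have no repeat value at all. It becomes most only with two or more values.
- A reader might infer that event rates differ several-fold, or that CRAS patients are tested more often so that the hazard ratio merely reflects testing. Neither follows: no treatment rate and no testing frequency is given.
- The Secondary outcomes rule is not free of difficulty. It also sets no minimum fall, still requires a follow-up haemoglobin that a phone call cannot supply, and speaks of needing treatment rather than receiving it.
- The scope is limited. The primary outcome, the baseline objectives, mortality and heart failure hospitalization are untouched. The continuous label also sits on hospitalization and worsening renal function, so it is a fault of the whole table.

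What does not stand is any suggestion that the conflict comes from condensation or text extraction. Both sentences are complete and the connecting words differ. A separate analysis plan might choose one rule, but one of the two published definitions would still be wrong.

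**Conclusion.** The contradiction is established by the text alone: an untreated fall in haemoglobin is an event in Table 3 and a non-event in the Secondary outcomes section. Followed as written, Table 3 also turns chance fluctuation into events and makes event status depend on how often haemoglobin is rechecked. The size of that effect is conditional on exchangeable readings, on the assumed SDs, and on a number of rechecks that the protocol leaves open. The difference in event counts and the direction of any group bias cannot be determined from the documents. This should be fixed, but as it affects one of four secondary outcomes it does not threaten the main objectives.

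**What to change.** Reconcile the Secondary outcomes section and Table 3 to one event definition before outcomes are coded, and do not let a bare fall of any size count as a Cox event. The treatment-linked wording of the Secondary outcomes section already meets that condition, provided it states whether need means receipt of transfusion or erythropoietin recorded during follow-up. State also how the fall is established for patients contacted only by phone.

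In Table 3, relabel the variable dichotomous, analysed as time to first event. If laboratory change is of interest in itself, report it descriptively in g/dl among patients with a follow-up haemoglobin, with the number who have one in each group.

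The cost is a few lines of wording. The downside is fewer events than under Table 3, and so less precision for this outcome.

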### Study variables

#### Objective 1

Aim to determine the prevalence of cardiorenal anemia syndrome among patients with heart failure irrespective of ejection fraction at baseline Table 1.

**Table 1 pone.0292764.t001:** Summary and description of objective number 1 variables of the study.

Variable	Method of measurement	Operational definition	Level of measurement
CRAS	Patient assessment/medical or echocardiographic records/blood sample	Heart failure with ejection fraction of <50% or >50%, chronic kidney disease with estimated glomerular filtration rate <60mil/min/1.73m^2^ and anemia with hemoglobin of <13 g/dl for men or <12 g/dl for women	Dichotomous

#### Objective 2

Aims to determine the clinical correlates for the cardiorenal anemia syndrome at baseline among the patients with heart failure irrespective of ejection fraction [2, 6, 24, 25]. Information from medical records such as chronic kidney disease using serum creatinine level and echocardiographic report will be accessed from 18^th^ February, 2023 onwards. Table 2.

**Table 2 pone.0292764.t002:** Summary and description of variables for the objective number 2.

Variable	Method of measurement	Operational definition	Level of measurement
**Age**	Medical records/patient	Age in years	Continuous
**Gender**	Medical record/patient report	Male versus female	Dichotomous, categorical
**Alcoholic use**	Patient report, interview	Use of alcoholics regardless of amount/units, years or number of drinks per day	Dichotomous, categorical
**Anemia**	Blood sample	When hemoglobin level is <13 g/dl for men or <12 g/dl for women	Dichotomous, continous
**Iron deficiency**	Blood sample	Serum ferritin of <100μg/l and high sensitive C-reactive protein of ≥3 mg/dl; or serum ferritin of 100 to 300 μg/l and calculated transferittin saturation (TSAT) of < 20% will indicate iron deficiency	Dichotomous, continous
**Hypertension**	Medical records/patient report/ patient assessment	Known hypertensive patient from records; or measurement of BP readings by conventional method using digitalized calibrated Blood pressure machine adhered on standard operating procedures and when the average of last two readings taken in between 3 minutes apart is ≥ 140/90mmHg will indicate hypertension	Dichotomous, categorical
**Chronic kidney disease (CKD)**	Medical records/patient report	Known patient with CKD from medical records within 6 months retrospectively prior enrollment or when estimated GFR is <60mil/min/1.73m2 by CKD-EPI formula using serum creatinine level	Dichotomous, continous
**Dyslipidemia**	Medical records/patient report/blood sample	Evidence of dyslipidemia on medications from records or for unknown lipid status, when the total cholesterol ≥200 mg/dl, low-density lipoprotein cholesterol ≥130 mg/ dl, and high-density lipoprotein cholesterol < 40 mg/ dl for men or < 50 mg/ dl for women, and/or serum triglyceride level ≥150 mg/ dl	Dichotomous, categorical
**Diabetes**	Medical record/patient report/blood sample	Known patient with diabetes mellitus on medications from records or for unknown status, is when the random blood glucose is ≥11.1 mmol/L and glycosylated haemoglobin of ≥6.5%	Dichotomous, categorical
**Electrolyte imbalance**	Medical report/blood sample	Serum Na+ of <135mmol/L or >145mmol/L and/or serum K+ of < 3.5mmol/L or >5.5mmol/L	Continous
**Obesity**	Medical record/patient assessment	When the waist circumference of >94 cm for males or >88 cm for females; or calculated waist-hip ratio (WHR) of >0.9 for men or of >0.8 for women	Dichotomous, categorical

#### Objective 3

Aims to determine the outcomes of the cardiorenal anemia syndrome among the patients with heart failure within six months follow up period [2, 5, 7, 11, 25] Table 3.

**Table 3 pone.0292764.t003:** Summary and description of variables for the objective number 3.

Variable	Method of measurement	Operational definition	Level of measurement
**All-cause mortality**	Medical records or close relative through phone contact	Any death occurs within six month follow up irrespective of the cause of death	Dichotomous
**Heart failure hospitalization**	Medical record/patient report/assessment	admission of which cause-specific is heart failure	Continuous
**Worsening renal function**	Medical record/patient report/blood sample	When there is a change in Chronic kidney disease stage or a need of dialysis or both	Continuous
**Worsening anemia**	Medical record/patient assessment/blood sample	Change of hemoglobin level to lower level from baseline or a need of blood transfusion or erythropoietin use or both	Continuous

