*Lipid profile*. Dyslipidemia is defined as total serum cholesterol ≥200 mg/dL, or LDL-cholesterol ≥130 mg/dL, or serum triglyceride ≥150 mg/dL, or HDL-cholesterol <40 mg/dL for women and <50 mg/dL for men [16, 33].

*Blood sugar measurement*. Diabetes mellitus will be defined as either known patient with type 1 or 2; and for unknown diabetic status, is when random blood glucose by using blood from finger prick is ≥11.1mmol/L and glycated hemoglobin is ≥6.5% [14, 34].

*Iron studies*. Iron deficiency will be defined as serum ferritin of <100μg/l and high sensitive C-reactive protein of ≥ 3 mg/dl [35], or serum ferritin of 100 to 300 μg/l and transferittin saturation (TSAT) ≤ 20% [7, 10–12, 36].

*Full blood picture*. Anemia will be defined when hemoglobin ≤ 12g/dl for women or ≤ 13g/dl for men. Mean Corpuscular Volume (MCV) and Mean Corpuscular Hemoglobin (MCH) will be recorded to characterize the type of anemia [2, 12, 16].

*Serum electrolytes*. Electrolyte imbalance will be considered when the serum sodium is ≤ 135 mmol/l (hyponatremia) or ≥ 145mmol/l (hypernatremia) and / or potassium level of ≤ 3.5mmol (hypokalemia) or ≥ 5.3 mmol/l (hyperkalemia) [20, 33, 37].

*Blood creatinine*. Chronic kidney disease will be defined following estimation of glomerular filtration rate. Glomerular Filtration Rate will be calculated by using CKD-EPI formula by adjustment of African-American correction factor and value of <60mil/min/1.73m2 will be considered as chronic kidney disease [34, 37, 38].

*Two-dimension transthoracic echocardiogram (2D-TTE)*. Transthoracic Echocardiography (model Vivid TM T9 manufactured by GE Healthcare, USA 2018) will be used for recommended patients who are either newly diagnosed patients or for previous known HF patients of which their echocardiogram reports are of more than 6-months prior to index contact. Transthoracic Echocardiogram will be done by experienced echocardiographer and/or confirmed by consultant cardiologists. Depending on condition of the patient so, a patient will be instructed to undress and expose the chest then, the patient will lie on the left lateral decubitus position and then, change to supine position during imaging for different echocardiogram views. The imaging will take 10 to 20 minutes.

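### Worsening anaemia has two conflicting definitions, one of which can count erythropoietin already in use at entry as an event; the haemoglobin-only anaemia definition needs a sensitivity analysis for treated patients

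*Protocol article*

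**What the plan says.** **Worsening anaemia.** The protocol article defines this secondary outcome in two places. Under Clinical outcomes, Secondary outcomes, it is a drop in haemoglobin below the baseline level that then requires transfusion, erythropoietin or both. Under Study variables, Objective 3, Table 3, a drop in haemoglobin is one alternative and treatment is another: "a need of blood transfusion or erythropoietin use or both". Table 3 does not say that the treatment must be new since baseline.

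**Anaemia at baseline.** Every definition is a haemoglobin cut-off with no clause for treated cases. The Primary outcome section has "anemia of <12 g/dl for women or <13 g/dl for men". Table 2 has "When hemoglobin level is <13 g/dl for men or <12 g/dl for women", with a blood sample as the only source. The laboratory section has "Anemia will be defined when hemoglobin ≤ 12g/dl for women or ≤ 13g/dl for men", which also differs at the boundary value.

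**Other conditions in Table 2.** Several count known or treated cases whatever the index measurement: "Known hypertensive patient from records" for hypertension, "Known patient with CKD from medical records within 6 months retrospectively prior enrollment" for CKD and "Evidence of dyslipidemia on medications from records or for unknown lipid status" for dyslipidaemia. Diabetes is handled in the same way.

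**Exclusions and groups.** The exclusion that refers to anaemia treatment covers CKD stage 5 on iron; the same item excludes renal replacement therapy. Bleeding, haemoglobinopathies and malignancy under chemotherapy or radiotherapy are also excluded. The Data analysis section then divides everyone into CRAS or non-CRAS.

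**The concern.** Worsening anaemia should record a change after baseline. Under Table 3, a patient who enters on erythropoietin and simply continues can be scored as having worsened, and so can a patient with any fall in haemoglobin, however small and untreated. Under the Secondary outcomes text neither is an event. Two analysts working from the same article could produce different event counts, and the Cox model for this outcome would inherit the difference. If erythropoietin use at entry differs between the CRAS and non-CRAS groups, the comparison would partly reflect treatment at entry.

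The related question is where treated patients sit at baseline. A patient with heart failure and CKD before stage 5 who has been transfused, or who takes iron or erythropoietin, can enrol. If the index haemoglobin is at or above the cut-off, that patient is non-CRAS. Recruitment includes the nephrology department, where such treatment is plausible. Prevalence and all outcome comparisons use this grouping, so the reader needs to know how far the results depend on it.

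**Working it through.** **Step 1: the two event definitions applied to the same patients.**

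| Course after baseline | Secondary outcomes text | Table 3 |
|---|---|---|
| On erythropoietin at entry, continues, haemoglobin unchanged | No event | Can be an event |
| Haemoglobin falls, no treatment needed | No event | Event |
| Haemoglobin falls, transfusion or erythropoietin newly needed | Event | Event |

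The definitions agree only on the third row. The first row is the one in which nothing has changed.

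**Step 2: who can be treated and eligible.** After the exclusions listed above, these patients remain eligible: those on erythropoietin without renal replacement therapy, those recently transfused for a reason that is not itself an exclusion, and those on iron before CKD stage 5. They enter the non-CRAS group only if their haemoglobin is at or above the cut-off.

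**Step 3: possible effect on prevalence.** The plan has no figure of its own to reproduce here. Inputs: expected prevalence of 40% (Sample size estimation); minimum sample of 300 (Data collection process); *t*, the share of true CRAS patients treated to or above the cut-off, which is an assumption. Here true CRAS means CRAS with treated anaemia counted as anaemia.

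Measured prevalence = 0.40 × (1 − *t*). Share of the non-CRAS group that is treated CRAS = 0.40*t* / [1 − 0.40(1 − *t*)].

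| *t* | Patients moved, of 300 | Measured prevalence | Share of non-CRAS group |
|---|---|---|---|
| 5% | 300 × 0.40 × 0.05 = 6 | 38% | 0.02/0.62 = 3.2% |
| 10% | 12 | 36% | 0.04/0.64 = 6.3% |
| 20% | 24 | 32% | 0.08/0.68 = 11.8% |

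**Step 4: direction of bias for worsening anaemia under Table 3.** Assume true six-month risks of 30% (CRAS) and 15% (non-CRAS), a risk ratio of 2.0. Take *t* = 5%, with half of the moved patients on erythropoietin and scored as events.

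- Non-CRAS risk = [0.60 × 0.15 + 0.02 × (0.5 + 0.5 × 0.30)] / 0.62 = 0.103/0.62 = 0.166.
- If no CRAS patient is on erythropoietin at entry: 0.30/0.166 = 1.81, towards no difference.
- If 20% of CRAS patients are also on it at entry and scored as events (assumption): CRAS risk = 0.30 + 0.20 × 0.70 = 0.44, and 0.44/0.166 = 2.65, away from no difference.

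The sign depends on treatment frequencies that the article does not give.

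**The case against.** A reader might infer that treated patients are misclassified CRAS cases, that the primary definition is therefore wrong, and that the outcome comparisons are pulled towards no difference. The documents do not support this.

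- Objective 1 concerns prevalence at baseline, and a haemoglobin cut-off is a coherent definition of current CRAS. The triad also sets CKD by a measured eGFR threshold. Iron deficiency, the closest variable in kind, is likewise taken from a blood sample with no treated-case clause. The contrast with hypertension, diabetes and dyslipidaemia is real, but those are correlates and not components of the triad.
- Dilution of the mortality and admission comparisons would require treated patients to keep a CRAS-like prognosis, which nothing in the article establishes. For worsening anaemia, step 4 shows that the bias can go either way.
- Changing the primary outcome after 92 enrolments would loosen the link to the earlier study that supplied the 44.4% comparator.
- It cannot be said that prior anaemia treatment goes unrecorded. The questionnaire is not shown, and its stated content includes underlying comorbid conditions.

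All of this stands, and it rules out calling the haemoglobin definition an error. On worsening anaemia, the defence is that the Secondary outcomes text already prevents continuing erythropoietin from counting, and that the word *need* in Table 3 might be read as a new need. The first part is correct for that section. It does not settle the matter, because Table 3 is the operational definition for Objective 3, contradicts that text, and does not say that the need must be new.

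**Conclusion.** The conflict over worsening anaemia is established from the text alone and needs no assumption. As long as Table 3 stands, erythropoietin already in use at entry, or any fall in haemoglobin, can be counted as an event that the Secondary outcomes section would not count.

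The baseline point is smaller. Classing anaemia on index haemoglobin is acceptable as the primary definition, but the exclusions leave room for treated patients in the non-CRAS group, so the dependence of the results on that choice should be shown. The size and direction of any effect are unknown, because the article gives no frequency of prior anaemia treatment. The fall from 40% to between 38% and 32% rests wholly on the assumed range of 5% to 20% treated above the cut-off; the true share could be lower.

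**What to change.** 1. Reconcile the Secondary outcomes text and Table 3 into one definition of worsening anaemia. State whether a fall in haemoglobin alone qualifies. Count transfusion or erythropoietin as an event only when newly started or newly needed after baseline.
2. Record transfusion, erythropoietin and iron use at baseline, if the questionnaire does not already do so, using the medical records that the study already accesses (from 18 February 2023 onwards).
3. Keep the haemoglobin definition of anaemia as primary. Add a sensitivity analysis that counts documented, treated anaemia as anaemia, for prevalence and for the CRAS versus non-CRAS outcome comparison. Use one boundary rule throughout, since the sections differ between < and ≤.

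The cost is a reworded definition, at most one questionnaire item, and one sensitivity analysis. The 92 patients already recruited when the article was written would need some record review. Their treatment histories may be incomplete, because the hospital takes patients from several regions, and the number with unknown status should be reported.
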